### Implementation evaluation component

In accordance with a hybrid type I implementation-effectiveness approach, we will employ a mixed-methods implementation evaluation utilizing the Practical, Robust Implementation and Sustainability Model (PRISM) [57, 58]. The primary objective of the implementation evaluation is to understand the implementation determinants (i.e. barriers and facilitators), contextual factors and corresponding implementation strategies that support successful reach, adoption, implementation, and sustainability of the SIRI team intervention.

Implementation outcomes will be evaluated by conducting qualitative participant exit interviews (post-intervention only) and key informant interviews (pre- and post-intervention implementation). Specific EHR data (e.g., socio-demographics, co-morbidities) will also be included in the implementation analyses to assess the characteristics of participating patients. Outcomes include: reach (e.g., number of those eligible who engage in the study, baseline comparisons between those who decline versus those who accept participation), effectiveness at the patient level (i.e., the primary outcome), adoption at the staff level (e.g., number and proportion of physicians who agree to refer patients to the study, barriers to staff-level adoption), implementation (e.g., fidelity to the intervention manual, implementation cost analysis) and maintenance (e.g., cost-effectiveness, budget impact/cost savings, facilitators of long-term intervention use).

Participant exit interviews will be conducted with participants from both the intervention and control groups at all 6 sites, with anticipated samples of 10–15 participants per study group (approximately 20–30 participants per site). These brief exit interviews (approximately 30 minutes) will occur at the conclusion of each participant’s intervention period in a private room by a trained study team member at each individual site. These designated site interviewers will be trained by the Implementation team Co-Investigators prior to interview initiation and will follow the interview guide. To capture the PRISM domain of “Patient Perspective (Receptiveness to SIRI Team, Satisfaction),” guide items include participant’s satisfaction with the SIRI team plus any considerations related to intervention adaptation. All participants will receive compensation upon completing the interview (suggested amount is $50, but the amount and method, e.g., gift card/cash, will be determined based on local standards).

Key informant interviews will be conducted with a sample of 36–48 key informants (6–8 per site) at two time points: 1) prior to study launch and 2) post-intervention (near the time that the intervention period has closed for the last participant at a given site). Given the objective of gathering qualitative data to examine barriers to staff-level adoption, key informants include any study personnel deemed critical to the intervention development and implementation, such as physicians, nurse practitioners, physician assistants, and case managers. Interviews will be scheduled based upon key informant schedule and availability, and interviewees will be consented to participate in both qualitative interviews prior to initiation. The interviews are brief (approximately 45–60 minutes) and open-ended. One of the Implementation team co-investigators conducts the interviews either by teleconference or videoconference (e.g., Zoom). All participants receive an Amazon gift card in the amount of $50 upon completing the interview.

### Economic evaluation

The trial includes a comprehensive economic evaluation to estimate the cost and cost-effectiveness of the SIRI team intervention relative to TAU from the healthcare sector, state policymaker, and societal perspectives. The primary outcome for the economic evaluation is the incremental cost-effectiveness ratio (ICER), which is defined as the incremental mean cost of the SIRI team intervention relative to TAU divided by the incremental mean effectiveness [59]. Program costs will be determined using a microcosting approach and identifying the resources used by sites to implement and sustain the intervention, through site visits, interviews with program staff, and review of study records [60, 61]. Participant data will be measured through electronic health record data collected on case report forms, as well as self-reported data collected via the Non-study Medical and Other Services (NMOS) instrument [62–66]. Costs will be estimated using the resource-costing method, wherein each resource unit consumed/utilized will be weighted by a nationally-representative, inflation-adjusted dollar value intended to reflect the real-world costs faced by decision-makers aligned with each perspective.

Three measures of effectiveness will be utilized in the cost-effectiveness analysis. The primary measure of effectiveness is the quality-adjusted life-year (QALY). Health-related quality of life (HRQoL) will be measured at each time point using the Patient-Reported Outcomes Measurement Information System (PROMIS)-Preference (PROPr) instrument. We will additionally evaluate opioid-free years, a measure of opioid use frequency, which has long been used in economic evaluations of OUD care [67, 68]. As the HI-SIRI trial also includes participants without OUD, we will also utilize a similar measure of time free from IDU. These measures will be constructed using a combination of urine drug testing results and participant self-report.

### Statistical analysis

#### Sample size and power analysis for efficacy outcome

Effect size was estimated for fixed power and sample size using PASS 2020. Since the true proportion of success in each treatment group is unknown, effect size was calculated for 80% power, a sample size of 480, and varying proportions of success in the TAU treatment group from 0.35 to 0.70 in steps of 0.05. Effect size was estimated using a logistic regression model for a binomial outcome with a logit link. The stratification factors used at randomization (site, type of primary drug use and admission to ICU as part of the index hospitalization) were not included in the power calculation model and therefore the power estimates are conservative. However, the stratification factors will be included in the analysis model at the analysis stage as fixed effects to improve the precision of the estimates. Table 3 shows the estimated effect size for varying proportions of success in the TAU treatment arm. The resulting risk differences and odds ratios corresponding to the proportions of success are also included for interpretation of the varying effect sizes. For a sample size of *N* = 480, there is 80% power or more for an absolute risk difference of 12.8% regardless of the level of success in TAU.

**Table 3 Tab3:** Power calculations for primary outcome based on potential rates of success in treatment as usual group

Sample Size	Power	Proportion of Success in		Risk	Odds
		TAU	SIRI team	Difference	Ratio
480	0.80	0.350	0.476	0.126	1.684
		0.400	0.527	0.127	1.672
		0.450	0.578	0.128	1.669
		0.500	0.627	0.127	1.678
		0.550	0.674	0.124	1.695
		0.600	0.721	0.121	1.721
		0.650	0.766	0.116	1.764
		0.700	0.810	0.110	1.825

SIRI, severe injection-related infection; TAU, treatment as usual

#### Analyses of primary and secondary outcomes

A logistic regression model will be employed: alive and no hospital readmission (excluding elective treatment/procedures, detoxification-only or psychiatric admissions to a specialty hospital) OR any hospital readmission or death since previous visit as implemented in SAS. The test of the primary hypothesis will be achieved using the Wald test associated with the coefficient on the treatment indicator with the outcome at the 4-month follow-up. The model will include fixed effects for treatment group, site, type of primary drug use (opioid versus non-opioid), and admission to ICU as part of the index hospitalization (ICU versus non-ICU). The primary outcome hypothesis that the proportion of participants alive with no hospital readmissions will be higher in the SIRI Team intervention group vs. TAU group at four months post-randomization will be evaluated using a two-sided test with an a priori alpha (i.e., type I error) of 0.05. Since odds ratios can exaggerate interpretation of relative risk, particularly with larger incidence of the outcome, a Poisson distribution with log link and robust standard errors may also be considered to estimate the risk ratio directly.

For the primary outcome, data lost to missed visits will be supplemented via external records. Confirmation of death from any cause or of participant hospital readmission from the EHR abstraction will be considered a failure. If a participant is lost to follow-up and no records (EHR, medical examiner, emergency contacts’ report) are found to show death or readmission for the duration of the study, the outcome will be considered a success. Missing data is only anticipated for 1) participants who withdraw from the study up to and including study day 122 and who have not signed the consent addendum expressly permitting abstraction to continue, or 2) participants who withdraw from the study at any time during the follow-up period AND who have not signed the consent addendum AND EHR abstraction has not been performed up to and including study day 122 prior to the participant’s withdrawal. At baseline, participants will sign releases for all local health systems that they typically visit. These records will be supplemented by a query of EHR integration services, such as CareEverywhere in Epic Systems. For participants who miss their 4 month visit but attend the 8 or 12 month visit, they will be asked about readmissions dating back to the time of randomization.

A secondary analysis of the hospital readmissions across all time points will be conducted. For this analysis, a Generalized Estimating Equations (GEE) model will be employed with a binomial distribution and logit link as implemented in SAS for the secondary outcomes of proportion of participants alive with no hospital readmissions utilizing all time points. A GEE model is used to control for correlation associated with repeated measures within an individual since the analysis will be a longitudinal one at 4-, 8-, and 12-months. The model will include fixed effects for treatment group, time, the treatment-by-time interaction, site, type of primary drug use (opioid versus non-opioid), and admission to ICU as part of the index hospitalization (ICU versus non-ICU)). The secondary outcome hypotheses are that the proportion of participants alive with no hospital readmissions will be higher in the SIRI Team intervention group vs. TAU group at eight months (and, separately, at twelve months) post-randomization). These two hypotheses will be evaluated each using a two-sided test with an a priori alpha (i.e., type I error) of 0.05.

Additional secondary analyses will utilize the methods for the primary analysis if they are a single dichotomous outcome. If they include repeated measures, they will follow the analysis strategy of the above secondary outcome description.

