## Methods/Design

### Study design and objectives

The HI-SIRI study is a multicenter non-blinded randomized controlled trial funded by NIDA and conducted in the National Drug Abuse Treatment Clinical Trials Network at 6 hospitals across the U.S. with two parallel treatment arms. The study aims to test the efficacy of an integrated infectious diseases (ID)/substance use disorder (SUD) clinical team intervention on improving health outcomes for PWID hospitalized with SIRIs. The SIRI team provides joint infectious diseases and addiction medicine expertise in a single care team. Participants are identified from the pool of inpatient admissions at participating hospitals. If medically stable, they are invited to provide written informed consent for a brief screening interview. If they screen eligible, provide written informed consent for full study participation, and provide HIPAA Authorization for medical record review, participants complete a baseline assessment (interview, urine drug screening, and medical record abstraction) and are randomized before hospital discharge. Randomization is stratified by 1) hospital site, 2) primary drug (opioid versus non-opioid), and 3) admission to ICU as part of the index hospitalization (ICU versus non-ICU). Participants assigned to the SIRI team meet with SIRI team members approximately daily while hospitalized and approximately weekly post-discharge over the 4-month-long intervention period. The intervention team provides care for infectious diseases and SUD, harm reduction services, patient navigation focused on SUD and social determinants of health, and general medical services throughout the intervention period. Participants assigned to treatment as usual (TAU) receive care and referrals as typically offered in the hospital setting at each site, which might include infectious disease, psychiatry, or addiction medicine consults during hospitalization. Study visits are conducted at baseline, 4 months, 8 months, and 12 months following randomization. The study protocol follows the Standard Protocol Items: Recommendations for Interventional Trials (SPIRIT) Statement (Appendix A). The study was reviewed and approved by the University of Miami Institutional Review Board (UM; IRB#20221134) which serves as the single IRB for the trial and provides regulatory oversight over all the participating sites. The study protocol is available in Appendix B.

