The primary objective of the trial is to determine whether the integrated ID/SUD care team intervention (SIRI team) will be associated with lower mortality and fewer hospital readmissions compared to TAU. The primary hypothesis is that the proportion of participants alive with no hospital readmissions will be higher in the SIRI team intervention group vs. TAU group at 4 months post-randomization. Secondary objectives are to examine differences between the two study groups in important milestones that may contribute to post-discharge recovery, harm reduction, and sustained health: proportion of participants alive with no hospital readmissions at all time points (4, 8, and 12 months post-randomization) to ascertain whether differences maintain during follow-up, completion of antibiotic course, initiation of treatment of SUD by hospital discharge, receipt of outpatient care post-discharge, retention in or completion of outpatient care, and change in substance use severity and frequency. Because the primary outcome is broadly defined as no hospital readmission and being alive (compared to any hospital readmission or all-cause mortality), we will examine more detailed sources of differences between the two groups as secondary outcomes: all-cause mortality, drug use-related mortality (infections or overdose), recurrent SIRI, and hospital readmission and emergency department visit number, type, and length. Additionally, the study’s economic evaluation will estimate the cost required to implement and sustain the SIRI team intervention and determine the relative value of the intervention from the healthcare sector and societal perspectives. The study’s simulation modeling will use healthcare utilization and health outcome data to estimate the long-term clinical- and cost-effectiveness of the intervention at a population-level. The objective of the implementation evaluation component is to understand preliminary determinants and strategies that lead to successful reach, adoption, implementation, and sustainability of the SIRI team intervention.

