### Outcomes

The primary outcome is a binary measure: a participant is alive with no hospital readmissions 4 months (122 days) post-randomization OR a participant has died or been readmitted to the hospital within 4 months post-randomization. The primary outcome measure is the proportion of those who are alive with no hospital readmission at 4 months post-randomization in the SIRI team intervention compared with TAU. Hospital readmission is defined as either observation or inpatient status in an acute care hospital after discharge from the index hospitalization (i.e., the hospitalization during which randomization occurred). Elective hospital admissions, for example, for planned chemotherapy or elective surgeries, are excluded. Hospital admissions for delivery of a child in pregnant participants will be included as elective admissions. Admission to behavioral health hospitals, medically supervised withdrawal units, or psychiatric-only admissions are also excluded. The primary outcome was chosen to be relevant to patients and healthcare systems. Healthcare utilization outcomes, such as readmission and emergency department visits, will be measured using both EHR data and self-report, confirmed by EHR. At baseline assessment and each follow-up study visit, participants will be asked about healthcare service utilization and if they report receipt of services, a release of information for each relevant institution will be obtained and records requested to confirm self-report. All participants will have the EHR of the study site (*index hospital*) healthcare system queried for health services use. Additionally, any integrated health information exchange services, such as Care Everywhere for Epic, will be queried. Deaths will be determined from EHR data, local medical examiner databases, and information from emergency/secondary contact persons for participants who cannot be located. The secondary outcome related to the primary outcome of the study includes being alive and free from readmission across all study time points (4, 8 and 12 months). Other secondary outcomes are listed in Table 2.

**Table 2 Tab2:** Key secondary outcomes

Outcome	Measure	Time point
Completion of planned antibiotic course	Combination of medical record abstraction and self-report	Assessed at 4-month visit
New or recurrent SIRIs	Combination of medical record abstraction and self-report	4, 8, and 12 months

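### Failure is counted since the previous visit in the analysis section but from randomization in the outcome definitions, so the 8- and 12-month secondary analyses have no single event window

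*Protocol article*

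**What the plan says.** The protocol article describes the event window in several places.

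- **Outcomes.** Primary failure means that "a participant has died or been readmitted to the hospital within 4 months post-randomization", with 4 months fixed at 122 days. A readmission counts only after discharge from the index hospitalization. The related secondary outcome is "being alive and free from readmission across all study time points (4, 8 and 12 months").
- **Study design and objectives.** The secondary objective counts 4, 8 and 12 months from randomization and asks whether differences are maintained. The schedule is: "Study visits are conducted at baseline, 4 months, 8 months, and 12 months following randomization".
- **Analyses of primary and secondary outcomes.** The sentence that introduces the logistic model writes the failure category as "any hospital readmission or death since previous visit". Later in the section, "a Generalized Estimating Equations (GEE) model will be employed with a binomial distribution and logit link", for 4, 8 and 12 months, without restating the window. Its hypotheses are set "at eight months (and, separately, at twelve months) post-randomization". Participants who miss the 4-month visit but attend a later one are told to look back further: "they will be asked about readmissions dating back to the time of randomization".

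The same section sends other repeated secondary outcomes to the GEE strategy. Table 2 lists several binary ones at 4, 8 and 12 months, including recurrent infection, non-fatal overdose, and any readmission or ED visit.

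**The concern.** A window that restarts at each visit and a window that always starts at randomization define different outcomes once there is more than one follow-up visit. The first asks whether the participant stayed well during the latest four months. The second asks whether the participant has stayed well since entering the trial. The article's written rule points to the first; its objective, outcome and hypotheses point to the second.

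Two secondary hypotheses, each tested at 0.05, depend on the choice, and so does the reading of the treatment-by-time term. In a non-blinded trial, leaving the choice until the data are in hand would give the analyst freedom over the claim that the benefit lasts.

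**Working it through.** **1. The two windows side by side** (visit schedule from Study design and objectives)

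| Row | Since previous visit | From randomization |
|---|---|---|
| 4 months | baseline visit to 4-month visit | randomization to day 122 |
| 8 months | 4-month visit to 8-month visit | randomization to month 8 |
| 12 months | 8-month visit to 12-month visit | randomization to month 12 |

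In the first row the windows nearly coincide. No extra event can enter at the start, because participants are inpatients at randomization and a readmission must follow index discharge. At the end, an event between day 122 and a later-held 4-month visit would count under one wording and not the other.

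**2. What happens to individual participants at month 8**

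- Readmitted in month 2, alive, not readmitted in months 4 to 8: success by interval, failure cumulatively.
- Died in month 3: failure cumulatively. Read literally, the interval rule gives no category: the participant is not alive, but the death is not since the previous visit. The article does not say how this row is handled.
- Missed the 4-month visit: if the previous visit means the last one attended, the interval runs back to baseline, twice the length used for others.

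**3. The plan's own figure.** Table 3 row 0.500 vs 0.627, two-sided 0.05, with 240 per arm (1:1 allocation is an assumption). The mean proportion is 0.5635.

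z = [0.127 × √240 − 1.96 × √(2 × 0.5635 × 0.4365)] / √(0.500 × 0.500 + 0.627 × 0.373) = (1.967 − 1.375) / 0.696 = 0.85, so power is 0.803.

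All eight rows give 0.798 to 0.803. Table 3 concerns month 4 and is not in dispute.

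**4. Illustration at later visits.** The article gives no 8- or 12-month rates. Assume the same Table 3 row at month 4, no treatment effect afterwards, and success c = 0.8 in each later interval, in both arms and regardless of earlier events.

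*Cumulative* (success at month 4 × c for each later interval):
- Month 8: 0.500 × 0.8 = 0.400 vs 0.627 × 0.8 = 0.502. Risk difference 0.102, power about 61%.
- Month 12: 0.500 × 0.64 = 0.320 vs 0.627 × 0.64 = 0.401. Risk difference 0.081, power about 46%.

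*Interval, earlier deaths left out:* 0.8 vs 0.8. Risk difference 0 at both times.

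*Interval, earlier deaths kept as failures* (assumed 6% vs 3% dead by month 4): 0.94 × 0.8 = 0.752 vs 0.97 × 0.8 = 0.776. Risk difference 0.024, power about 9%.

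For c from 0.7 to 0.9, the cumulative difference is 0.089 to 0.114 at month 8 and 0.062 to 0.103 at month 12. The interval difference with deaths kept as failures is 0.021 to 0.027.

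**5. Sensitivity to independence.** Suppose interval success is c₁ after an event-free first period and c₂ after an early event, equal in both arms. Month-8 success by interval is p·c₁ + (1 − p)·c₂, where p is month-4 success. The interval risk difference is then 0.127 × (c₁ − c₂), against 0.127 × c₁ cumulatively. Dependence narrows the gap, but the two agree only if c₂ = 0.

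**The case against.** The strongest reply is that the phrase appears only in the logistic-model sentence, while the GEE paragraph does not use it and words its hypotheses from randomization. The cumulative window is explicit only at day 122; at 8 and 12 months it is the natural reading, not a literal definition. This is fair. But with one post-baseline row the phrase has little to do; it acquires a distinct meaning only with repeated visits, and no other coding of the later rows is given.

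It can also be said that row-level coding belongs in the full protocol or SAP. That would answer an omission. Here the article states a rule, and the rule conflicts with its own definitions.

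Interval coding is also a defensible answer to whether differences are maintained, because a cumulative outcome carries month-4 differences forward by construction. This stands, and it is a reason to keep an interval analysis under its own label.

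Some stronger readings are tempting but unsupported:

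- *The primary test is compromised.* It is not, for the reasons in step 1 of the working.
- *The later tests compare survivors only.* Nothing says that deaths leave later rows, and the GEE outcome requires being alive. Only if they were dropped would the comparison be restricted to survivors.
- *Early readmission also leaves selected groups.* It does not: readmitted participants stay in the denominator under either coding.
- *The codings differ by some 38 points at month 12.* With constant, independent interval success of 0.55, 0.55 − 0.55³ = 0.384. That is a difference in level within an arm, not a bias in the treatment contrast.

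**Conclusion.** The point holds as a moderate defect limited to secondary analyses: the 8- and 12-month GEE comparisons and the other repeated binary outcomes that follow the same strategy. The interval rule and the post-randomization definitions conflict and are not reconciled in the article. The primary analysis and Table 3 stand, apart from visit date versus day 122.

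On the stated assumptions the month-8 risk difference is about 0.10 under one coding and about 0 to 0.03 under the other, so the same data could support different statements about durability. These sizes rest on 1:1 allocation, an assumed c, no effect after month 4, independence between intervals and assumed early mortality. None of these comes from the article, and the figures show scale only.

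**What to change.** Delete the words about the previous visit. Then state:

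1. **Primary outcome:** any qualifying event from randomization (for readmissions, after index discharge) through study day 122, whatever the date of the 4-month visit.
2. **GEE outcome:** cumulative status from randomization at fixed study days for months 4, 8 and 12, with readmission or death carried forward as failure.
3. **Other repeated binary outcomes:** the window used for each.
4. **If an effect after month 4 is also wanted:** a separately labelled supportive interval analysis that keeps all randomized participants and scores earlier deaths as failures in every later interval.

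The cost is wording in one section. Records are already abstracted to about 14 months after randomization, so no new data collection should be needed. The drawback is that the cumulative outcome does not isolate a post-intervention effect; item 4 covers that.

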**Screening**					
Demographics	X				
Housing Instability	X		X	X	X

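### The primary model is valid and adequately powered, but adjusting for a few more baseline variables that the trial already collects would be a cheap, optional gain in efficiency

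*Protocol article*

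**What the plan says.** The primary analysis is a logistic regression with a Wald test on the treatment coefficient, "evaluated using a two-sided test with an a priori alpha (i.e., type I error) of 0.05". Its covariate list is closed: "The model will include fixed effects for treatment group, site, type of primary drug use (opioid versus non-opioid" and ICU admission during the index stay. The sample size section gives the reason for adjusting: "the stratification factors will be included in the analysis model at the analysis stage as fixed effects to improve the precision of the estimates".

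Power was worked out without covariates: "effect size was calculated for 80% power, a sample size of 480", with "varying proportions of success in the TAU treatment group from 0.35 to 0.70 in steps of 0.05". The summary is that "there is 80% power or more for an absolute risk difference of 12.8% regardless of the level of success in TAU".

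Other baseline information is available:

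- Table 1 lists "Housing Instability" at screening.
- The Outcomes section states: "At baseline assessment and each follow-up study visit, participants will be asked about healthcare service utilization".
- The section on measures and timing adds comorbid conditions and service use to the interview.
- The study design section places the baseline interview and record abstraction before randomization.
- Boxes 1 and 2 require a confirmed or suspected qualifying infection for entry.

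None of these variables enters the primary model.

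**The concern.** Eligibility is very broad. Box 2 runs from cellulitis and sinus infection to prosthetic valve endocarditis, epidural abscess and central nervous system infection. ICU admission is the only marker of severity in the model. Because the outcome is readmission or death, infection type, earlier admissions and unstable housing are natural candidate predictors. In the pilot described in the Background, 71% of patients were homeless at admission.

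If the purpose of adjustment is precision, stopping at the stratification factors may leave some unused. Sample size is fixed, and the Discussion expects that practice may spread into the control arm and dilute the effect. At stake are a modest amount of power and some protection against chance imbalance in infection severity. The validity of the test is not in question.

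**Working it through.** **Inputs.** Two-sided alpha 0.05, N = 480 and the eight pairs of proportions come from the protocol article (Table 3 and the analysis section). The article gives no allocation ratio, so 1:1 (n = 240 per arm) is assumed. It gives no prognostic strength for any baseline variable, so every strength below is an assumption.

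**1. Reproducing the stated power.** For two proportions without continuity correction:

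power = Φ{ [d√n − 1.96√(2p̄(1−p̄))] / √(p₁(1−p₁) + p₂(1−p₂)) }

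For 0.450 vs 0.578: d√n = 0.128 × 15.492 = 1.983; 1.96 × √0.4996 = 1.385; denominator √0.4914 = 0.701. Then Φ(0.598/0.701) = Φ(0.852) = 0.803. All eight rows give 0.798 to 0.803. The unadjusted Wald test on the log odds ratio gives 0.793 to 0.799. The planned power therefore does not depend on any covariate.

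**2. Room for more covariates.** The smaller outcome class is the lesser of 240(p₁+p₂) and 480 − 240(p₁+p₂).

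- At 0.450 vs 0.578: 480 − 246.7 = 233.
- At 0.600 vs 0.721: 480 − 317.0 = 163.
- At 0.700 vs 0.810: 480 − 362.4 = 118.

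The range over Table 3 is 118 to 233. The planned model uses 1 (treatment) + 5 (six sites) + 1 (drug) + 1 (ICU) = 8 degrees of freedom. Four infection groups, prior admission and housing add 3 + 1 + 1 = 5, making 13. That leaves 118/13 = 9 to 233/13 = 18 participants in the smaller class per coefficient.

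**3. Gain over an unadjusted model.** Simulation with 4,000 trials per setting and one standard normal baseline score, with marginal proportions held at Table 3 values. Simulation error is about 0.6 points.

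| Odds ratio per SD (AUC) | Power, 0.450 vs 0.578 | Power, 0.600 vs 0.721 | Conditional odds ratios |
|---|---|---|---|
| 1.35 (0.58) | 0.792 → 0.800 | 0.798 → 0.808 | 1.69; 1.74 |
| 1.65 (0.64) | 0.810 → 0.827 | 0.808 → 0.832 | 1.73; 1.77 |
| 2.12 (0.69) | 0.806 → 0.848 | 0.809 → 0.848 | 1.79; 1.83 |
| 2.72 (0.74) | 0.804 → 0.873 | 0.807 → 0.869 | 1.86; 1.92 |

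**4. Gain over the model actually planned.** This is the relevant comparison, because site, drug and ICU are already adjusted for.

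*Stratification model, then with the score added* (2,000 trials per setting, modest assumed effects of the stratification factors). Log odds ratios per SD of 0.3, 0.5, 0.75 and 1.0 correspond to the four rows above:

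- 0.450 vs 0.578: 0.81 → 0.81, 0.81 → 0.84, 0.81 → 0.85, 0.82 → 0.88.
- 0.600 vs 0.721: 0.81 → 0.82, 0.81 → 0.82, 0.80 → 0.84, 0.81 → 0.87.

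*Stratification model, then with the three named covariates added* (4,000 trials per setting). Assumed prevalences are housing instability 70%, prior admission 40% and four equal infection groups. Odds ratios are for housing / prior admission / infection extremes:

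- 1.3/1.5/1.5 (AUC 0.58): 0.811 → 0.814 at TAU 0.50; 0.812 → 0.816 at TAU 0.60.
- 1.5/1.8/1.8 (AUC 0.61): 0.817 → 0.826; 0.814 → 0.826.
- 2.0/2.5/2.5 (AUC 0.67): 0.823 → 0.854; 0.807 → 0.842.

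**5. What the gain is worth.** Going from 0.80 to 0.84 power equals a sample size ratio of (1.960 + 0.994)²/(1.960 + 0.842)² = 1.112, or about 54 participants on 480. For comparison, if dilution cut the effect by 10% (an illustration; the article gives no figure), power would be about Φ(0.9 × 2.802 − 1.960) = Φ(0.562) = 0.71.

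**6. Effect on the target.** The fitted odds ratio becomes conditional on more covariates and moves away from Table 3's marginal values (1.669 and 1.721 for these two rows), as the last column of the table shows. The standardized risk difference does not drift: its simulated mean was essentially unchanged (for example 0.127 and 0.127). Its variance fell by about 2% with the weak score and 16 to 18% with the strong one.

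**The case against.** The strongest reply is that nothing here is wrong. The model contains exactly the factors that the sample size section promises, and it is prespecified. It reaches its power unaided, and that power is 80% by construction because the effect was solved for. The sample size section itself calls the figures conservative. Adjusted supplementary analyses may also stand in an analysis plan that is not shown. All of this stands. A reader might infer that the trial is underpowered or the model faulty, and the documents support neither.

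A reader might also take the covariates to be strongly prognostic and expect power of 0.85 to 0.87. No figure in the article supports that. Part of severity is already captured by ICU admission, and three crude variables may add little.

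Nor is the change free. It spends degrees of freedom, alters the conditional odds ratio and needs definitions that the article does not give. No look-back window for earlier admissions is stated.

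Infection type carries a specific hazard. Entry allows a suspected infection, and the section on SIRI team inpatient care has that team assist with diagnosis in the intervention arm. A classification updated after randomization could therefore be affected by treatment, and adjusting for it could bias the estimate. The article also does not show that infection type is stored as a coded baseline field. These objections shape the fix. They do not remove the benefit of adjusting for variables frozen before randomization.

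**Conclusion.** The point holds as an optional, low-cost efficiency improvement and not as an error. Beyond the stratification factors, the expected power gain is under 1 point at AUC about 0.58, about 1 to 2 points at 0.61 to 0.64, and about 3 to 4 points at 0.67 to 0.69. Individual simulated settings scatter around these values; one at AUC 0.64 showed 3 points. Larger gains need prognostic strength that nothing in the documents supports.

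In a logistic model the benefit shows as power of the Wald test. It appears as precision, the protocol's stated aim, once a marginal risk difference is reported.

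The figures assume 1:1 allocation, Table 3 proportions, the listed covariate strengths and prevalences, and no missing baseline values.

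**What to change.** Before unblinded data are seen, add to the primary model:

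- qualifying infection group (for example endovascular; bone, joint or central nervous system; skin and soft tissue; other), as classified and recorded before randomization and never updated, with a fixed hierarchy for overlapping diagnoses;
- any hospital admission within a stated look-back before the index stay, as recorded at baseline;
- housing instability at screening;
- a simple rule for missing baseline values, identical in both arms.

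Report the standardized risk difference with its confidence interval, so that the target stays the difference in proportions. Keep the stratification-only model as a sensitivity analysis. Table 3 needs no change.

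The cost is a few sentences of specification, about 5 degrees of freedom against 118 to 233 participants in the smaller outcome class, a standardization step, and a note that the fitted odds ratio is not comparable with Table 3. Enrolment and follow-up are unaffected. If infection group was not coded before randomization, leave it out.
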